### Interventions

For patients in the ta-VNS group, transcutaneous stimulation will be performed at the bilateral auricular concha with two pairs of stimulation electrode clips via the ear vagus nerve stimulator (TENS-200, Suzhou, Jiangsu, China) [7]. The stimulation electrodes are made of conductive rubber, with a diameter of 5 mm. The anode electrode is placed on the concha cavity and the cathode electrode is placed on the cymba concha. For patients in the tan-VNS group, transcutaneous stimulation will be performed at the marginal area of the auricle, which is not innervated by the ABVN. The parameters of the stimulation are as follows: frequency of 20 Hz; intensity of 1.0 mA; duration of 30 min; three times a day; and for a total of 6 months. Professional technicians will train the patients or their guardians about the use of the stimulators; patients then take the stimulators home and initiate the stimulators as needed.

For the control group, no transcutaneous stimulation is provided during the 6 months.

### Outcome measures

#### Primary outcomes

Seizure frequency: the baseline seizure frequency and the seizure frequency after 2 months, 4 months and 6 months of enrollment will be counted according to the patient’s seizure diary. Seizure outcomes will be expressed with a modified Engel scale [12].

#### Secondary outcomes

Video electroencephalogram (EEG): video EEG of each patient will be recorded for 2 hours before ta-VNS initiation and at the end of ta-VNS, respectively.

Heart rate variability (HRV): HRV of each patient will also be recorded before ta-VNS initiation and at the end of ta-VNS, respectively.

Health-related quality of life (QOL): parent’s perceptions of the child’s general behavioral problems will be quantified by using the total score of Achenbach’s Child Behavior Checklist (CBCL) [13]. The CBCL for ages 1.5–5 years and for ages 6–18 years are 99-item and 118-item questionnaires, respectively, and assesses behavioral problems in children. The guardians of the patients will be asked to rate whether a behavioral problem is present or not in the child and to what degree.

Side-effects or adverse outcomes: information about adverse outcomes will be recorded in the diary by the patient or their guardian. If a possible side-effect or adverse reaction occurs, the patient or their guardian should discontinue the stimulation and contact the doctor who will make a judgment. If serious side-effects occur, the doctor can then unblind the participant and give the patient post-trial care. All side-effects will be recorded and reported.

Detailed information about the whole schedule is summarized in Table 1.

**Table 1 Tab1:** Detailed schedule of the protocol

Schedule	Baseline	Treatment phase			Follow-up phase	
	0 months	2 months	4 months	6 months	1 year	1.5 years
Patients						
Informed consent	×					
Medical history	×					
Physical examination	×					
Randomization	×					
Intervention						
ta-VNS group	Transcutaneous stimulation at the auricular concha					
tan-VNS group	Transcutaneous stimulation at marginal area of the auricle					
Comparison						
Control group	No transcutaneous stimulation is provided					
Outcomes						
Seizure frequency	×	×	×	×	×	×
EEG	×			×		
HRV	×			×		
QOL	×			×		
Safety						
Adverse events	×	×	×	×	×	×

The symbol ‘x’ is used as a check mark

*EEG* electroencephalogram; *HRV* heart rate variability; *QOL* quality of life; *ta-VNS* transcutaneous auricular vagus nerve stimulation; *tan-VNS* transcutaneous auricular non-vagus nerve stimulation

### Quality control and trial monitoring

Before the initiation of the trial, the researcher will formulate an investigator’s brochure, standard operating procedures and detailed research plan. All the staff should participate in special training, including enrolling patients, completing the case report form and usage of the stimulator. The data monitoring committee has been established, which is independent from the sponsor and competing interests. Monitors will check case report forms at the participating hospitals once a month. Drop-outs and withdrawals (and the reasons) from the study will be fully documented throughout. All the data, including the case report forms and electronic documents, will be kept by special staff. The trial sponsor (BZ) has access to the final trial dataset.

The final report will follow the Consolidated Standards of Reporting Trials (CONSORT) extension guideline for non-pharmaceutical interventions. In order to minimize 6 months’ attrition, first we will enrol patients whose guardians can understand the mechanism of the ta-VNS treatment and our previous results. Second, in the consent inform, the participant and their guardian will be informed that the patient can get doctor consultation during the whole study period. They can also get a physical examination (EEG and HRV) and an auricular vagus nerve stimulator for free when they complete the study. The doctor will keep in touch with the patients once a month by phone or email. Additional file 1 describes the protocol in more detail.

### Statistical analysis

The intention-to-treat population will be defined as the participants who are randomized and received at least one treatment session. An interim analysis will be performed on the primary endpoint when 50 % of patients have been randomized and have completed the 1.5 years’ follow-up. The interim analysis will be performed by an independent statistician, blinded for the treatment allocation. All statistical calculations will be performed using SPSS v.17.0. Comparison of seizure frequency, HRV and QOL between baseline and after treatment will be analyzed by paired-samples t-test. The Kolmogorov-Smirnov test will be used to evaluate if groups fit normal distributions. Normally distributed groups will be analyzed by parametric tests. Comparisons between the three groups will be analyzed by one-way ANOVA followed by Student–Newman–Keuls or Dunnett’s T3 post-hoc tests. Non-normally distributed groups will be analyzed by Mann–Whitney’s test. The factors that affect curative effect will be analyzed with the multinomial logistic regression method. A *P* value <0.05 will be considered of statistical significance.

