### Randomization and blinding

Participants will be randomly assigned to either one of the two stimulations or the control group with a 1:1: sqrt(2) allocation, as per a computer generated randomization schedule stratified by the study center using permuted blocks of random sizes. The block sizes will not be disclosed, to ensure concealment. We will use Zelen’s design, in which randomization occurs before informed consent. Those patients in the control group (n = 42) receiving standard care will not be consented for participation in this study. They will be informed in an observational study with questionnaires to provide the same measurements, except for treatment, as that in the treatment groups for free, and thus blinded. Other participants who accept the intervention will provide further informed consents, in which they will be informed to have the possibility of receiving either one of the two stimulations according to computerized randomization schedule. The two stimulation groups will include the tan-VNS group (n = 30) and the ta-VNS group (n = 30). Participants in the control group and stimulation groups are thus blinded.

The randomization sequence will be generated using SPSS v.17.0 software (IBM, Armonk, NY, USA) and distributed in a sealed envelope to the doctor. The researchers will not be permitted to change it after the patients are randomized. Employees outside the research team will feed original data into the computer in separate datasheets so that the researchers can analyze data without having access to information about the allocation. The evaluation of the curative effect and the statistical analysis will be evaluated by a third party in the clinical evaluation center of the China Academy of Chinese Medical Sciences who will not know the grouping and patients. In this clinical trial process, the patients, statisticians and the assessor for statistical data and outcomes will be blind to treatment allocation. Allocation concealment will not be exposed until the final data analysis report is completed.

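### The population labelled intention-to-treat requires a treatment session, which no control receives and which removes post-randomization decliners from the stimulation arms only

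*Protocol article*

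**What the plan says.** The Statistical analysis section gives one definition of the main population, with no exception for any arm: "The intention-to-treat population will be defined as the participants who are randomized and received at least one treatment session". The same section plans a one-way ANOVA across the three groups.

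Under Interventions, the third arm is described thus: "For the control group, no transcutaneous stimulation is provided during the 6 months". Randomization and blinding agrees. It gives the control group 42 patients and says of them: "They will be informed in an observational study with questionnaires to provide the same measurements, except for treatment, as that in the treatment groups". Table 1 also lists the control group as receiving no stimulation.

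On the order of events, Randomization and blinding says: "We will use Zelen’s design, in which randomization occurs before informed consent". Families allocated to stimulation are asked for a further consent, which only those who accept provide. It tells them that either stimulation is possible. The article gives no expected refusal rate and does not say how families who refuse at that step are analysed.

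**The concern.** There are two problems, and they differ in weight.

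The first is an internal contradiction. A patient who is never offered a session cannot meet a condition that requires one. The population as defined contains no controls, so the planned three-group test cannot be run on it.

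The second remains after the wording is read generously. Suppose the session condition is meant only for the arms that have sessions. Then membership of the analysed stimulation arms depends on what families do after allocation: whether they accept, and whether they start a device that they operate at home. Controls are not put through that filter. In a design that randomizes before consent, refusal after allocation is to be expected. Keeping refusers in their allocated arm is what preserves the randomized comparison. A set that removes them from one side only, yet is called intention-to-treat, would lead readers to trust the stimulation-versus-control contrast more than it deserves.

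**Working it through.** **Inputs from the article.** Arms of 30 (ta-VNS), 30 (tan-VNS) and 42 (control), and allocation 1:1:sqrt(2), all from Randomization and blinding. Controls have zero sessions (Interventions, Table 1). The total is not stated; it is 30 + 30 + 42 = 102.

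**Inputs assumed.** Refusal or never starting, d = 10 to 30%. Outcome difference between acceptors and decliners, D = 0.25 to 0.5 SD. The article gives neither.

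**1. The plan's own figure.** Control size from the ratio: 30 × sqrt(2) = 42.43, stated as 42. The arm sizes are reproduced.

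**2. Literal reading.** Excluded automatically: 42/102 = 41.2%. Remaining at most: 60/102 = 58.8%, all in the stimulation arms.

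**3. Session condition applied to the stimulation arms only.** Retained = 42 + 60 × (1 − d), taking 30 and 30 as numbers randomized:

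| Assumed d | Stimulation patients kept | Total kept of 102 |
|---|---|---|
| 0% | 60 | 102 |
| 10% | 54 | 96 |
| 20% | 48 | 90 |
| 30% | 42 | 84 |

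**4. Shift with no treatment effect.** Write the mean of all randomized to stimulation as (1 − d) × m_acc + d × m_dec. The mean of the acceptors then departs from it by d × (m_acc − m_dec) = d × D. If the control group represents everyone randomized to it, this is the bias in stimulation versus control:

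| Assumed d | D = 0.25 SD | D = 0.5 SD |
|---|---|---|
| 10% | 0.025 SD | 0.05 SD |
| 20% | 0.05 SD | 0.10 SD |
| 30% | 0.075 SD | 0.15 SD |

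As d approaches 0 the shift approaches 0.

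**5. Scale.** The standard error of a 60-versus-42 comparison is sqrt(1/60 + 1/42) = 0.20 SD. A shift of 0.10 SD is about half of that.

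**6. ta-VNS versus tan-VNS.** Families deciding on stimulation are told that they may receive either kind. Refusal at that step should therefore be unrelated to which one was allocated, and the argument in step 4 does not carry over to this contrast.

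**7. After the fix.** All randomized, as allocated: 30 + 30 + 42 = 102 of 102 at any d.

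**The case against.** **The controls will obviously be analysed.** This stands as to intent. The three-group test, the matching measurements collected from controls and Table 1 all show that the arm is meant to be compared. A reader might infer from the definition that 42 patients will be lost; the documents do not support that. The 41% describes the rule as worded, not a foreseeable loss.

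**Controls are filtered too.** This stands in part. A reader might infer that consenting starters will be compared with unselected all-comers, but controls are told of an observational study and may decline it. The article is also inconsistent on their consent. Study design says consent is sought from all guardians of participants, and inclusion criterion 5 requires a signed consent, yet Randomization and blinding says: "Those patients in the control group (n = 42) receiving standard care will not be consented for participation in this study". If criterion 5 bound every arm, decliners might be called ineligible. But eligibility settled by a decision taken after allocation is itself post-randomization selection. The two steps also ask for different things: acceptance of a device in one case, completion of questionnaires in the other. Selection on both sides would not be expected to cancel, though the one-sided model in the working is a simplification.

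**The bias is assumed, and modest against sampling error.** This stands. No refusal rate or prognostic gap is given, and few refusals would make the shift negligible. Unlike sampling error, however, the shift is systematic, and the results cannot reveal it if decliners are not followed.

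**The sham comparison is spared.** This largely stands, for the reason in step 6. A reader who took the whole trial to be compromised would be going too far.

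**It is not a per-protocol set.** Correct. One session imposes no adherence or completion requirement, so treated-only or modified intention-to-treat is the accurate name.

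**The 30 and 30 may count acceptors.** Possible, since those figures follow the sentence on families who accept. Decliners would then lie outside the 102, and the number randomized to stimulation would be 60/(1 − d): about 67, 75 and 86 at 10, 20 and 30%. The counts in step 3 change; the shift d × D does not.

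**Conclusion.** The definition is wrong as written and needs correcting. Its literal form excludes the whole control arm and contradicts the analysis planned in the same section; this needs no assumption and is most likely a drafting slip. Its generous form is a treated-only set under an intention-to-treat label, with different post-allocation filters for stimulation and control.

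The resulting bias in stimulation versus control is of unknown size. The range of 0.025 to 0.15 SD rests wholly on the assumed refusal rates and prognostic gaps and on selection acting on the stimulation side alone. The documents do not show that it would change the trial's result. The ta-VNS versus tan-VNS contrast is largely unaffected.

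This is not a matter of detail left to an analysis plan: the article fixes the definition explicitly, and the definition conflicts with the trial's own arms and randomization design.

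**What to change.** - Define the intention-to-treat population as all randomized participants, controls and decliners included, analysed in the arm to which they were allocated.
- Keep the session condition only for a separately named secondary or safety set, limited to the two stimulation arms.
- Offer families who decline stimulation, and who agree, the diary and questionnaires already used for controls. Report by arm how many decline and how many of those have no outcome data.

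The wording change is one sentence. The follow-up costs more: it is an added collection step that depends on the agreement of families who have already refused something. Recruitment had reached 35 by 15 February 2015, so outcomes of earlier decliners may not be recoverable and will have to be treated as missing. The stimulation-versus-control estimate is also diluted in proportion to refusal. If decliners receive no stimulation and 20% decline, the expected contrast is about 1 − 0.20 = 0.80 of the effect in acceptors.

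### The between-group test is selected by a Kolmogorov-Smirnov result on each group, so ta-VNS and sham can fall on different sides of the rule and the plan does not say which test then applies

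*Protocol article*

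**What the plan says.** Protocol article, Statistical analysis, sets the selection rule in three sentences:

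- "The Kolmogorov-Smirnov test will be used to evaluate if groups fit normal distributions".
- "Normally distributed groups will be analyzed by parametric tests".
- "Non-normally distributed groups will be analyzed by Mann–Whitney’s test".

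Between the second and third it adds: "Comparisons between the three groups will be analyzed by one-way ANOVA followed by Student–Newman–Keuls or Dunnett’s T3 post-hoc tests". The significance threshold is a P "value <0.05 will be considered of statistical significance".

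Randomization and blinding gives the sizes to which the rule applies. "Participants will be randomly assigned to either one of the two stimulations or the control group with a 1:1: sqrt(2) allocation"; there are 30 children in each stimulation group and 42 in the control group.

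Under Primary outcomes, seizure frequency is counted from diaries and is then to be expressed on a modified Engel scale. Entry requires at least eight seizures in 2 months (Inclusion criteria), and no upper limit is given.

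**The concern.** All three sentences of the rule take the single group as their unit, whereas every comparison of interest takes two or three groups. Three things are left open:

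- **Mixed result.** If one arm passes and the other fails, the ta-VNS v sham comparison belongs to both branches or to neither.
- **Non-normal branch.** Mann–Whitney compares two samples. No three-group rank test is named, and nothing says how the pairwise tests would be combined.
- **Parametric branch.** Two post-hoc procedures are joined by the word or, with no criterion for choosing.

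Seizure counts with a floor at entry and no ceiling are likely to be right-skewed, so failures of the normality test should be expected. The outcome of that test also depends on group size: 42 controls are rejected more often than 30 children drawn from the same distribution. What is at stake is that the test behind the main efficacy result is not fixed before the data are seen, and in a split the analyst holds two defensible P values.

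**Working it through.** **Plan's own figure.** 30 × √2 = 42.43, which rounds to the stated 42; 30 + 30 + 42 = 102. The sizes agree with the allocation ratio.

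**Inputs from the article.** Groups 30/30/42; baseline count at least 8; threshold 0.05 (two-sided assumed).

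**Assumptions (not in the article).** Each child's 2-month rate is lognormal with median 20 and log-rate SD 0.8 or 1.0. Baseline and follow-up counts are Poisson with gamma overdispersion k = 5. Sham and control have rate ratio 1; ta-VNS has 1 (null) or 0.6 (40% reduction). 20,000 trials per setting.

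**Normality test.** With z = (x − mean)/SD sorted within a group, D = max over i of [i/n − Φ(z_i), Φ(z_i) − (i − 1)/n]. The article does not say which critical values apply, so both were used:

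- Lilliefors (simulated): 0.159 at n = 30, 0.135 at n = 42.
- Uncorrected: 1.358/√30 = 0.248 and 1.358/√42 = 0.210.

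**ta-VNS v sham at rate ratio 0.6**

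| | SD 0.8, Lilliefors | SD 0.8, uncorrected | SD 1.0, Lilliefors | SD 1.0, uncorrected |
|---|---|---|---|---|
| Pair splits | 25.2% | 36.6% | 12.9% | 48.4% |
| Splits, and t-test and Mann–Whitney disagree at 0.05 | 4.7% | 9.5% | 2.6% | 12.0% |
| Power, Mann–Whitney if either arm fails | 58.4% | 56.9% | 48.4% | 47.5% |
| Power, t-test if either arm passes | 57.5% | 49.8% | 47.7% | 38.8% |
| Power, fixed t-test on log(count+1) | 60.1% | 60.1% | 50.2% | 50.2% |

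Set against the fixed log-scale test at the same SD:

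- Mann–Whitney if either arm fails loses 60.1 − 58.4 = 1.7 to 60.1 − 56.9 = 3.2 points.
- t-test if either arm passes loses 50.2 − 47.7 = 2.5 to 50.2 − 38.8 = 11.4 points.

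**Type I error (rate ratio 1).** Taking the smaller P value only when the pair splits gives 5.3–6.1%.

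**Shorter runs of the same model** gave pair splits of 12–27% and 37–48%, split-and-disagree of 3–5% and 10–12%, log-scale power of 51–60%, and 5–7% error for the smaller P value in splits. The last figure is best read as about 6%.

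**Effect of group size.** Under the null at SD 0.8, a group of 42 is rejected in 45% of trials and a group of 30 in 24% (uncorrected); with Lilliefors the figures are 95% and 86%.

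**Dependence on shape.** With other assumed distributions the split rate moves widely:

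- Exactly normal data: the pair splits in 10% of trials (Lilliefors) or about 0% (uncorrected).
- Lognormal (sigma 0.3–1.2, some truncated at 8) and negative binomial shapes: 4–50% (Lilliefors) or 1–49% (uncorrected).
- A four-class ordinal outcome, standing in for the modified Engel scale: the three groups split in 0% (all fail, Lilliefors) or 63–71% (uncorrected).

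**Non-normal branch.** If Mann–Whitney is applied to all three pairs at 0.05 without adjustment, the family-wise error under the global null is about 11.5%.

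**The case against.** The strongest reply is that groups is loose wording for the data being compared, that a sensible analyst would use Mann–Whitney whenever either arm fails, and that a tie-break is the sort of detail left to the additional file or an analysis plan. Under that reading the cost is indeed small, 1–4 points of power. But the article does publish a selection rule, and the rule as written has no outcome for a mixed result. Even on the loose reading, the non-normal branch still names a two-sample test for three groups. The point is a badly fixed rule, not a missing detail.

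Several stronger inferences are not supported:

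- **That groups will often split.** The article gives no distribution, SD or test variant, and the rate runs from about 0% upward across plausible shapes.
- **That no valid comparison exists.** Each test alone is near nominal size: in the null runs, 4.1–4.6% for the t-test and 4.7–5.0% for Mann–Whitney. The fault is the open choice.
- **That the choice is made on unmasked data.** Randomization and blinding keeps the statistician blind to allocation until the final report is complete. The choice still depends on the data, but deliberate selection is harder.
- **That the tests disagree because of the rule in a fifth of trials.** Exactly one is significant in 20–23% of all trials at a 40% reduction, but most of these are not splits.
- **That the rule imposes the power of a raw-scale t-test (34–48%).** It sends groups that fail to Mann–Whitney, so that figure does not describe it.
- **That the normality check is misapplied to the paired t-test.** The article states the paired test without condition, before the normality sentence, and nothing clearly ties the two.

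**Conclusion.** The concern holds as a defect in the rule. The article selects the test group by group, gives no instruction when ta-VNS and sham differ, and names only a two-sample test for the non-normal case.

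The consequence is moderate. Under the assumed skewed counts, the open choice changes the verdict in about 3–5% (Lilliefors) or 10–12% (uncorrected) of trials with a real 40% reduction, and exploiting it in splits lifts the 5% error to about 6%. Power loss ranges from 1–4 points under the kindest reading to about 11 under the least kind. The quoted span of 39–58% reflects the assumed SD as well as the reading, so like must be compared with like: 50–58% against 60% at SD 0.8, and 39–48% against 50% at SD 1.0.

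These figures rest on an assumed count distribution and on analysing counts. They do not carry over to the modified Engel scale. The gap in the rule itself rests on the text alone.

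**What to change.** Remove the Kolmogorov-Smirnov test as a selector and keep distribution plots as description only. Name one between-group method per outcome, applied to all three groups whatever the normality result:

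- **Seizure counts:** a linear model on log(count+1), with the ta-VNS v sham contrast stated. Mann–Whitney on that pair is the single named sensitivity analysis.
- **HRV:** the same linear model, with skewed power measures on the log scale.
- **CBCL total score:** a linear model on the raw scale.
- **Modified Engel class, where it is the outcome:** one named ordinal method, such as a proportional-odds model.

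With one method fixed, a split cannot arise. The cost is wording in the statistical section and the analysis plan; no extra children or data are needed. It should be settled before the planned interim analysis of the primary endpoint, not merely before database lock. The downside is that effects on seizure counts are reported as ratios, and with the added 1 these only approximate rate ratios when many children reach zero seizures.

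### Student-Newman-Keuls is named for arms that are unequal by design (30:30:42); run with one common harmonic-mean n, it could test ta-VNS against sham at up to about 6.2% instead of 5%

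*Protocol article*

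**What the plan says.** The protocol article's section on randomization and blinding makes the arms unequal on purpose: "Participants will be randomly assigned to either one of the two stimulations or the control group with a 1:1: sqrt(2) allocation". It gives the resulting sizes as 30 for ta-VNS, 30 for tan-VNS (the sham) and 42 for control ("Those patients in the control group (n = 42) receiving standard care").

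The Statistical analysis section sends outcomes down one of two routes. "Normally distributed groups will be analyzed by parametric tests", and for these: "Comparisons between the three groups will be analyzed by one-way ANOVA followed by Student–Newman–Keuls or Dunnett’s T3 post-hoc tests". Outcomes judged non-normal go to Mann-Whitney. On software and level it says "All statistical calculations will be performed using SPSS v.17.0" and, of the P value, "value <0.05 will be considered of statistical significance".

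The article does not say how SNK is to handle unequal sizes, or when SNK rather than Dunnett's T3 applies.

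**The concern.** SNK orders the group means and compares each range with a studentized-range cut-off, using one standard error for all pairs. That is exact only when the groups are the same size. One way of carrying it over to unequal groups is to put a single average size, the harmonic mean, into every comparison. The two smaller arms are then treated as larger than they are, and those two arms form the ta-VNS versus sham contrast.

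That contrast matters most for interpretation. The end of the Background names tan-VNS as the sham comparator, so only ta-VNS against tan-VNS separates a vagal effect from the effect of having a device. A standard error that is too small makes a false claim on it more likely when both stimulation arms move away from control together.

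The gate in front of the post-hoc tests raises a second, smaller point. Dunnett's T3 is meant for unequal variances, yet it follows an ordinary one-way ANOVA, which assumes equal ones.

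**Working it through.** **Inputs.** From Randomization and blinding: ratio 1:1:√2; n = 30, 30, 42. From Statistical analysis: ANOVA then SNK or T3; level 0.05. Assumed, because the article is silent: SNK uses the harmonic mean of the three sizes. The alternative, each pair's own sizes, is shown beside it. Simulations use normal data.

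**The plan's own figure.** 30 × √2 = 42.4, rounded to 42; total 30 + 30 + 42 = 102. The sizes agree with the ratio. Residual df = 102 − 3 = 99.

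**Standard errors under the common size** (in units of the SD)
- Harmonic mean: 3 / (1/30 + 1/30 + 1/42) = 33.16.
- Common standard error: √(2/33.16) = 0.2456.
- Correct value for ta-VNS minus sham: √(2/30) = 0.2582. Ratio 0.2456/0.2582 = 0.951, so 4.9% too small.
- Correct value for stimulation minus control: √(1/30 + 1/42) = 0.2390. Ratio 0.2456/0.2390 = 1.027, so 2.7% too large.

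**Level of each SNK step.** The cut-offs at 99 df are 2.806 for two means and 3.365 for three; 2.806/√2 = 1.984, the ordinary t value.
- ta-VNS v sham, two-mean step: 2·P(t99 > 1.984 × 0.951) = 6.2%.
- ta-VNS v sham when they are the two extreme means: 2·P(t99 > (3.365/√2) × 0.951) = 2.6%.
- Stimulation v control, two-mean step: 2·P(t99 > 1.984 × 1.027) = 4.4%.

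**Full step-down procedure.** The 6.2% applies only when the procedure reaches the two-mean step, so the whole procedure was simulated: 1,000,000 trials per row, equal variances, ta-VNS equal to sham, control shifted. The table gives how often ta-VNS is declared different from sham.

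| Control shift | SNK, harmonic n | Same, after a significant F | SNK, pair's own sizes |
|---|---|---|---|
| 0 SD | 3.0% | 2.4% | 2.4% |
| 0.3 SD | 4.3% | 4.1% | 3.5% |
| 0.5 SD | 5.6% | 5.5% | 4.5% |
| 0.8 SD | 6.2% | 6.2% | 5.0% |
| 1 SD or more | about 6.2% | about 6.2% | 5.0% |

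The largest excess is 6.2 − 5.0 = 1.2 percentage points.

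**The overall F-test.** With all means equal and sizes 30/30/42 (200,000 trials per pattern), the ordinary F-test rejects in about 7.5% of trials if the ta-VNS SD is double the others, 7.4% if both stimulation SDs are double, and 3.8% if the control SD is double. Welch's test stays at about 5.0%. The variance patterns are illustrative; the article gives no SDs.

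**Does that F-test harm T3?** A pair declared after F and T3 must be significant by T3 itself, so the gate can only remove claims. In 200,000 trials per pattern, any false pair was declared in 3.1% (ta-VNS SD doubled), 4.0% (both stimulation SDs doubled) and 2.9% (control SD doubled). The sham contrast was declared in 1.7%, 1.7% and 0.3%.

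**The case against.** A reader might infer that the plan tests ta-VNS against sham at 6.2% as a matter of course. The document does not support that, for three reasons.

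- **SNK is one route among three.** Dunnett's T3 uses each pair's own sizes and variances, and Mann-Whitney does not use SNK at all. The primary outcome is a diary seizure count with an entry floor of eight in 2 months, expressed on a modified Engel scale. It may well be judged non-normal and never reach SNK.
- **The harmonic-mean size is an assumption about the software.** The article names the package, not the rule. With pair-specific sizes the simulated rate runs from 2.4% to 5.0%.
- **The 6.2% needs a large control difference.** Nothing in the article gives a sham-versus-no-stimulation effect or an SD, so a shift of 0.8 SD cannot be called likely. When all arms are equal, the rate is below 5%.

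A reader might also infer that the liberal F-test makes T3's pairwise findings unreliable. It does not: T3 after the gate is conservative, and the 7.4% to 7.5% belongs to the overall test alone.

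Finally, the rule for choosing SNK or T3, and the reporting of confidence intervals, may stand in the SAP or in the additional file. Their absence from the article is not held against the plan.

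What stands is that the article itself fixes both the unequal sizes and a test derived for equal ones. Under one way of running that test, the error goes in the anti-conservative direction on the sham contrast.

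**Conclusion.** The point holds as a conditional and minor one. If SNK is used with a common harmonic-mean size, and control differs from both stimulation arms by about 0.8 SD or more, the sham contrast runs at up to about 6.2%, an excess of at most 1.2 points. With smaller shifts the excess shrinks and then disappears, and with pair-specific sizes there is none. The result also assumes normal data with equal variances.

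The scenario is still worth guarding against: both stimulation arms departing from control while not differing from each other is the null that a sham arm is there to detect. The sensitivity of the F-test to unequal variances is real but affects only the overall test.

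**What to change.** For the parametric route, replace the ANOVA and the choice between SNK and T3 with:

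1. a Welch overall test of the three groups at 5%;
2. if it is significant, the three pairwise contrasts at 5%, each with its own group sizes and unequal-variance (Welch) standard error;
3. a 95% confidence interval for ta-VNS minus sham. SNK sorts means into subsets and does not supply one.

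With three groups no further multiplicity adjustment is needed. If all means are equal, any pairwise claim first requires a false overall rejection, at about 5%. If exactly one pair is equal, only that pair can be falsely claimed, again at about 5%. The family error therefore stays at about 5%, without relying on equal variances.

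Keeping T3 alone would also remove the SNK fault, but T3 is more conservative: 0.3% to 1.7% on the sham contrast in the simulations above.

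The cost is wording only, with no new data and no change to the sample size. The sham-contrast standard error becomes 0.2582/0.2456 = 1.051 times that of harmonic-mean SNK (with equal variances), about 5% larger, which is its correct size.
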